**Fig. 1 fig1:**
[figure not shown]
Design of the AMBER study: Inclusion criteria and endpoints. Patients should fulfill the indicated inclusion criteria to be eligible for this trial. * hemoglobin, ≥9.0 g/dL; white blood cell count, ≥12,000/mm^3^; absolute neutrophil count, ≥2000 cells/mm^3^; platelet count, ≥100,000 cells/mm^3^; normal kidney and liver functions as determined by creatinine, total bilirubin, aspartate transaminase (AST), and alanine transaminase (ALT) ≤2 × the upper limit of normal for the reference laboratory.

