**Fig. 2 fig2:**
[figure not shown]
Exclusion criteria of the AMBER study. Abbreviations: ALA, aminolevulinic acid; SFC, sodium ferrous citrate.

The use of α1-adrenoceptor antagonists to ameliorate post-seed urinary discomfort or prevent urinary retention is permitted. Prohibited medications and procedures are not set up in this trial. Medications before and after seed implantation should be recorded.

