### Determining the target sample size

2.4

To date, we have been working on several clinical studies regarding oncological outcomes, adverse events, complications, and changes in urinary frequency and PROs among patients undergoing LDR-BT [3,4,14,17,18]. In this study, the data of the trial cases will be compared with historical control data. Data of patients who underwent seed implantation monotherapy between February 2016 and February 2019 will be extracted for the historical control data. The primary endpoint of this trial is urinary frequency 3 months after the implantation. One of our previous studies showed that a significant increase in urinary frequency and significant decrease in mean voided volume persisted for 12 months after seed implantation [14]. The average times per day of urination increased from 9.2 at baseline to 12.2 at 3 months after seed implantation because of bladder irritability. This observation indicated that the increase in urinary frequency was 3 times per day at 3 months, which was the peak point. To determine the required sample size of this trial, we expect that oral ALA-SFC can suppress the increase in urinary frequency to only 1 time per day and estimate the standard deviation of urinary frequency to be 3.5 times both in trial cases and historical control cases. The ratio of case numbers is set to 1:3 for trial cases and historical control cases, respectively. Given the 10% proportion of ineligible patients, the required sample size was determined to be at least 37 for trial cases and 109 for historical control cases to provide 80% power (β = 0.20) and an α level of 0.05 (two-sided). Based on the estimation, a total of 50 trial cases and 150 historical control cases will be enrolled in this study. The historical data will be obtained from consecutive patients undergoing LDR-BT with or without short-term ADT between January 2016 and January 2019. Patients who received prophylaxis with 50 mg of mirabegron (a β3-adrenoceptor agonist) just after seed implantation for decreasing undesired urgency and urinary frequency will be excluded from the historical control cases. Patients who received supplementary extra-beam radiotherapy will be excluded from the historical control cases. Pre- and post-treatment clinicopathologic factors are compared between two groups: age, body mass index, comorbidities, pretreatment urinary frequency, pretreatment PSA level, pretreatment prostate volume, biopsy Gleason score, clinical tumor stage, D'Amico risk stratification, and the post-implant dosimetric parameters.

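### Apart from the EBRT and ADT rules, the eligibility criteria for trial cases are not applied to the historical controls, so the only comparison is between groups selected under different rules

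*Protocol article*

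**What the plan says.** **Trial cases.** The Fig. 1 legend states: "Patients should fulfill the indicated inclusion criteria to be eligible for this trial". It then lists limits for haemoglobin, white cells, neutrophils, platelets, creatinine, bilirubin, AST and ALT. A second list, Fig. 2, is titled "Exclusion criteria of the AMBER study"; its content is not visible here. Section 2.1 excludes supplementary EBRT and admits short-term neoadjuvant ADT.

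**Historical controls.** Section 2.4 says that monotherapy patients will be extracted, and then: "The historical data will be obtained from consecutive patients undergoing LDR-BT with or without short-term ADT between January 2016 and January 2019". Two exclusions follow. One is mirabegron prophylaxis just after implantation. The other is EBRT: "Patients who received supplementary extra-beam radiotherapy will be excluded from the historical control cases". The Abstract gives the same consecutive-patient definition. Neither place refers to Fig. 1 or Fig. 2.

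**Analysis.** Section 2.4 lists baseline and dosimetric factors to be compared between the groups, including comorbidities, pretreatment urinary frequency and PSA. Section 2.6 names Mann–Whitney, Wilcoxon, Fisher, Tarone and log-rank tests. It names no adjustment or matching.

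**The concern.** With an external control group, a difference at 3 months can be attributed to treatment only if the groups would have been alike without it. Using the same entry criteria for both is the first safeguard. As written, a man outside a Fig. 1 laboratory limit, or with a Fig. 2 exclusion, is refused as a trial case but counted as a control if he falls in the date window.

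If such men void more or less often than the rest, part of the difference in 3-month frequency comes from selection. An unadjusted test cannot separate that part from an effect of ALA-SFC. Adjustment would help only partly, because a type of patient barred from one group has no counterpart there. The listed factors also include no blood-count, renal or hepatic eligibility value. The historical controls are the only comparator, and the pilot's result is meant to inform a randomised trial.

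**Working it through.** **1. The rules side by side**

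| Criterion | Trial cases | Historical controls |
|---|---|---|
| Supplementary EBRT | excluded (2.1) | excluded (2.4) |
| Short-term ADT | allowed (2.1) | allowed (2.4) |
| Fig. 1 laboratory limits | required | not mentioned |
| Fig. 2 exclusions | required | not mentioned |
| Mirabegron prophylaxis | no prohibited medications (text after Fig. 2) | excluded (2.4) |

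The first two rows match. The defect lies in the third and fourth. The mirabegron row is a separate asymmetry.

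**2. The plan's own sample size**

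Inputs from section 2.4: "the increase in urinary frequency was 3 times per day at 3 months" without the drug; "oral ALA-SFC can suppress the increase in urinary frequency to only 1 time per day" with it, so the difference is 3 − 1 = 2; "estimate the standard deviation of urinary frequency to be 3.5 times both in trial cases and historical control cases"; ratio 1:3; 80% power; two-sided alpha 0.05; 10% ineligible.

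- The two-sample t-test solution is 32.54 trial cases and 97.61 controls.
- Dividing by 0.9 gives 36.15 and 108.46, rounded up to 37 and 109.

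The stated 37 and 109 reproduce exactly, so this point does not touch the sample size.

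**3. What a selection shift would do**

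At the planned 50 and 150:

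- SE = 3.5 × √(1/50 + 1/150) = 0.572
- Smallest significant difference = 1.96 × 0.572 = 1.12 voids/day

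With no drug effect and a shift b between the group means, the two-sided rejection probability is Φ(b/SE − 1.96) + Φ(−b/SE − 1.96). This is a normal approximation for a comparison of means, used as a guide to the planned rank test.

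| Assumed shift b (voids/day) | b/SE | False-positive rate |
|---|---|---|
| 0 | 0 | 5.0% |
| 0.02 | 0.03 | 5.0% |
| 0.09 | 0.16 | 5.3% |
| 0.2 | 0.35 | 6.4% |
| 0.4 | 0.70 | 10.8% |
| 0.6 | 1.05 | 18.3% |

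The shift equals the share of controls who would fail the trial criteria times their difference in voids/day from the rest. Neither figure is in the documents, so both are assumptions. A share of 1 to 3% with a difference of 2 to 3 gives 0.02 to 0.09. A share of 10 to 20% with the same difference gives 0.2 to 0.6. The formula is symmetric: a shift the other way gives the same rates, with the error against the drug.

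**4. What fewer controls would cost**

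With 50 trial cases and 109 controls, SE = 3.5 × √(1/50 + 1/109) = 0.598. Power for a difference of 2 is Φ(2/0.598 − 1.96) = 91.7%, against 93.8% with 150 controls.

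**The case against.** The strongest reply is that the article is silent on this rather than wrong. It condenses a full protocol that may define the controls further. The 10% ineligible allowance is built into the control figure of 109 as well as the 37, which suggests that some eligibility check of controls was foreseen. Some trial rules do carry over, and comorbidities and pretreatment frequency are to be compared, so a gross imbalance would be seen. The visible renal and hepatic limits, at twice the upper limit of normal, are fairly loose and may remove few men who were fit for implantation.

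Much of this stands, and it limits how strongly the point can be put. It does not remove it. Section 2.4 gives a population, a window and named exclusions, and it restates the EBRT exclusion for controls. That restatement would be unnecessary if the trial criteria carried over automatically. The 10% allowance names no criteria. Comparing baseline factors shows an imbalance but does not correct it.

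A reader might infer that screened, healthier trial cases are set against sicker, unscreened controls, and that the drug is therefore favoured. The documents do not support this. Fig. 2 and the Fig. 1 graphic are not visible, and nothing links the laboratory limits to voiding frequency. Nor does this problem offset the mirabegron exclusion. If mirabegron lowers frequency, removing its users from the controls alone would raise the control mean. A screening bias of the kind a reader might infer would do the same.

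**Conclusion.** The point holds as a difference in selection rules. As written, men outside the Fig. 1 limits or with Fig. 2 exclusions can be controls but not trial cases, and the stated tests do not correct for this. The direction of any bias is unknown. Its size depends on two figures the documents do not give: over the range shown, the false-positive rate runs from practically unchanged (5.0 to 5.3%) to 18.3%. These rates assume SD 3.5, 50 against 150 men, and a normal approximation.

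Severity is low to moderate: this is a pilot, and the effect may be negligible if few controls would fail the criteria. Confidence is moderate, because the figures are not visible and the full protocol may say more.

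**What to change.** In section 2.4, state that the historical controls must meet the same Fig. 1 and Fig. 2 criteria as the trial cases wherever these can be assessed from pre-implant records. Consent and items specific to ALA or SFC are left out. The criteria should be applied by someone without knowledge of the 3-month outcome. Report how many consecutive patients each criterion removes. Use the restricted group for the primary comparison and the full consecutive group as a sensitivity analysis.

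One item must be settled first. The Fig. 1 legend prints the white-cell limit as at least 12,000/mm³. Applied literally to controls, it would keep only men at or above that count, and the loss could be large. The sponsor should check and reconcile that limit before it is used.

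The cost is a wording change, a chart check and somewhat fewer controls. Whether the laboratory values are in the older charts is an assumption. The white-cell limit aside, the loss of precision is small: 109 controls suffice by the plan's own calculation, and with 50 trial cases they keep power near 92%.

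### Early mirabegron prophylaxis removes a patient from the historical controls, but no matching rule is stated for trial cases, although the drug targets the primary endpoint

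*Protocol article*

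**What the plan says.** **Controls.** Section 2.4 (Determining the target sample size) states that patients who had mirabegron prophylaxis "just after seed implantation for decreasing undesired urgency and urinary frequency will be excluded from the historical control cases".

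**Trial cases.** Section 2.1, in the text after Fig. 2, states: "Prohibited medications and procedures are not set up in this trial". It adds: "The use of α1-adrenoceptor antagonists to ameliorate post-seed urinary discomfort or prevent urinary retention is permitted". On other drugs it asks only for a record: "Medications before and after seed implantation should be recorded".

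**Endpoint and analysis.** "The primary endpoint of this trial is urinary frequency 3 months after the implantation". Section 2.6 (Statistical analysis) compares the groups with unadjusted two-group tests. The factors that section 2.4 lists for comparison between the groups do not include urinary medication.

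**The concern.** The article gives the purpose of the drug as lowering urgency and urinary frequency, and urinary frequency is the primary endpoint. Its early prophylactic users are removed from one side of the comparison only. The trial is open-label and not randomised, so nothing in the design keeps co-medication alike in the two groups, and the stated tests do not adjust for it.

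If some trial cases receive the same prophylaxis and it still lowers frequency at month 3, that reduction is counted as an effect of ALA-SFC. The result is meant to inform a later placebo-controlled trial, so an inflated estimate would carry forward into its planning.

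**Working it through.** **Step 1: reproduce the plan's own figure.** The inputs are all from section 2.4.
- Control change: "The average times per day of urination increased from 9.2 at baseline to 12.2 at 3 months after seed implantation", that is +3 per day.
- Trial change: it is expected that "oral ALA-SFC can suppress the increase in urinary frequency to only 1 time per day", so the planned difference is 3 − 1 = 2 per day.
- SD: the authors "estimate the standard deviation of urinary frequency to be 3.5 times both in trial cases and historical control cases".
- Two-sided α 0.05, power 80%, ratio 1:3, 10% ineligible.

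Normal approximation for the trial group: (1 + 1/3) × (3.5 × (1.960 + 0.842) / 2)² = 32.05. With the t distribution, 33 and 98 patients give a power of 0.805. Allowing for ineligible patients, 33/0.9 = 36.7, rounded up to 37, and 98/0.9 = 108.9, rounded up to 109. The stated 37 and 109 are reproduced. The sample size does not depend on the mirabegron rule.

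**Step 2: compare the two rules.**

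| | Historical controls (2.4) | Trial cases (2.1) |
|---|---|---|
| Mirabegron prophylaxis just after implantation | Excluded | Not prohibited; no exclusion visible |
| α1-blockers | No exclusion stated | Permitted |
| Other bladder drugs, or mirabegron started later | No exclusion stated | Not prohibited; recorded |

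The rules differ in the first row only: one drug, one purpose, one time point. Because controls with this prophylaxis are removed, the between-group difference in early prophylaxis equals its use among trial cases.

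**Step 3: possible size, by assumption.** The article gives neither the share of trial cases using the drug (p) nor its effect on frequency at month 3 (e). The assumed ranges are p from 0 to 50% and e from 0 to 2 per day.
- Bias b = p × e.
- SE with 50 and 150 patients = 3.5 × √(1/50 + 1/150) = 0.57 per day.
- With no true ALA-SFC effect, the chance of a two-sided p < 0.05 is Φ(−1.96 + b/SE) + Φ(−1.96 − b/SE). This treats the test as a comparison of means, as the sample-size calculation does.

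| Use p | Effect e (per day) | Bias b (per day) | Share of planned 2 per day | Type I error |
|---|---|---|---|---|
| 0, or any | any, or 0 | 0 | 0% | 5% |
| 10% | 0.5 | 0.05 | 2.5% | 5.1% |
| 20% | 1 | 0.2 | 10% | 6.4% |
| 20% | 2 | 0.4 | 20% | about 11% |
| 30% | 2 | 0.6 | 30% | about 18% |
| 50% | 1 | 0.5 | 25% | about 14% |
| 50% | 2 | 1.0 | 50% | about 42% |

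The t distribution gives 41% in the last row.

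**The case against.** **The exclusion list cannot be seen.** The trial exclusion criteria are in Fig. 2 and the discontinuation criteria in Fig. 4, and neither figure is shown. This stands as a limit: the absence of a matching rule can be claimed only for the visible text. However, a baseline criterion would not by itself cover a drug started after implantation, and the statement on prohibited medications points the other way.

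**The drug may not matter.** The Discussion says that the benefit of several drug classes, β3-adrenoceptor agonists among them, is not yet proven. This stands too. With no effect or no use, the bias is nil. It does not justify a one-sided rule: if the drug is irrelevant, the control exclusion is unnecessary, and if it is relevant, it is relevant in both groups.

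**Removing such controls is reasonable in itself.** Agreed. It gives a comparator free of another preventive drug, and a consecutive series may have stated exclusions. The problem is only that no like condition is stated for trial cases.

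**Analysis sets belong in a fuller document.** Often so, but this article does state who enters the control group, and the rule as stated applies to one side.

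**Two stronger readings are not supported.** A reader might infer that controls on any bladder drug are removed. The text removes only early mirabegron prophylaxis. A reader might also infer that the mismatch can only favour ALA-SFC. Controls who start bladder drugs later stay in, and if they use more of them by month 3, co-medication as a whole could work against ALA-SFC.

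**Conclusion.** Sections 2.1 and 2.4 treat early mirabegron prophylaxis differently in the two groups, and the difference bears on the primary endpoint. It can bias the unadjusted 3-month comparison toward ALA-SFC on two conditions: trial cases receive the drug, and it lowers frequency at month 3. The article shows neither.

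Under the assumed ranges the bias runs from nil to 1.0 per day. The figure of about 42% needs half the trial cases on the drug and an effect as large as the whole planned ALA-SFC benefit, so it marks the edge of the range and is not an expected error rate. At 20% use and 1 per day, type I error is 6.4%.

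Because the mismatch is narrow and its size unknown, this is a cheap improvement, not a defect that must be repaired before the trial can be used.

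**What to change.** Reconcile sections 2.1 and 2.4, and state the following in 2.4 or 2.6 before analysis:
1. The primary comparison set applies the same rule on mirabegron prophylaxis just after implantation to trial cases and controls.
2. Bladder-drug use up to month 3 is tabulated by group.
3. A sensitivity analysis repeats the primary comparison with no mirabegron exclusion in either group.

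These are analysis rules only. They change no patient's care and imply no view on which drugs should be given.

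The cost is a few sentences. Trial medications are already recorded. For controls the table needs the same information from their charts, and the article does not say how complete that is. If the common rule is an exclusion, a few trial cases may leave the primary set. Excluding patients for a treatment given after enrolment also carries some selection risk, and the sensitivity analysis is there to show whether it matters.

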### Inclusion criteria, patient recruitment, and study design

2.1

This prospective, single-center trial in patients with localized PCa is ongoing at Nara Medical University (a Japanese academic hospital). The trial design and protocol adhere to the Recommendations for Interventional Trials (SPIRIT) criteria. The completed SPIRIT checklist can be found in Supplementary data. Investigators and patients will be aware of the intervention of ALA-SFC. The flowchart, inclusion criteria, primary endpoint, and secondary endpoints are depicted in Fig. 1. Patients who undergo supplementary extra-beam radiotherapy (EBRT) are excluded, whereas those undergoing short-term (4–6 months) neoadjuvant androgen deprivation therapy (ADT) to decrease the prostate volume and/or improve oncological outcomes are included. As a general rule of our hospital, the combination of luteinizing hormone-releasing hormone agonist/antagonist and oral bicalutamide (80 mg/day) are used for neoadjuvant ADT. The exclusion criteria are listed in Fig. 2. Informed consent and written consent forms of patients are mandatory before study participation. After the screening and registration, the patients will be enrolled to a single treatment group of a fixed dose of oral ALA-SFC (200 mg and 229.42 mg per day). Subjects will undergo the seed implantation under spinal anesthesia and be instructed to take capsules of ALA-SFC twice a day for 6 months from the day of seed implantation.

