### Procedure of LDR-BT

2.2

As of November 30, 2019, we have an LDR-BT treatment experiment of more than 1400 patients. The detailed procedure of the seed implantation has been previously described [13,14]. All the patients are hospitalized for 3 nights and 4 days. The prescribed radiation dose is 160 Gy for the monotherapy. For patients without any contraindications, SpaceOAR™ hydrogel is injected between the rectum and prostate to minimize high-dose radiation to the rectum and consequent bowel side effects. Experienced radiation oncologists ([name] and [name]) calculate the post-implant dosimetric parameters based on a pelvic computed tomography scan performed about 1 month after LDR-BT.

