## Discussion

3

It has been more than 15 years since LDR-BT was introduced in Japan [2]. A comprehensive review reported excellent oncological outcomes showing equivalent or superior efficacy to radical prostatectomy for low- or intermediate-risk PCa and superiority for high-risk PCa based on the experience of more than 52,000 patients undergoing LDR-BT with or without EBRT [2]. However, there are still significant concerns about side effects, complications, and consequently reduced QOL after radiotherapy. One of our long-term interests is worsening lower urinary tract symptoms. Most urinary adverse events are categorized into grade 1 to 2, while higher-severity adverse events are rare. More than 70% of patients experience increased urinary frequency (pollakiuria) during the first 6 months after seed implantation [19]. To overcome this clinical issue, our group and other groups have conducted randomized controlled trials to explore medications preventing post-treatment urinary adverse events. However, the true benefits of α1-adrenoceptor antagonists, anti-cholinergic drugs, β3-adrenoceptor agonists, phytotherapeutic drugs, and non-steroidal anti-inflammatory drugs have not been proven yet [14,[20], [21], [22]].

We plan to evaluate whether oral ALA-SFC prevents GU toxicities after seed implantation. ALA-SFC is widely accepted as a health supplement and food with functional claims in Japan. This product reportedly inhibits elevations in blood glucose level, improves sleep quality, and supports muscle strength and exercise efficiency [23,24]. Moreover, preclinical studies have demonstrated that ALA confers cytoprotective effects in the bladder, rectum, kidney, heart, and neural system from various types of stress [7,[9], [10], [11], [12]]. Another potential benefit of adding ALA is an increase in the radiosensitization of malignant cells. Previous research has shown that ALA supplementation sensitizes malignant cells including glioma, melanoma, and colon adenocarcinoma cells to radiotherapy via enhanced generation of protoporphyrin IX and reactive oxygen species [7]. Our previous preclinical study confirmed that adding *in vitro* single and *in vivo* repeated administration of ALA sensitized PCa cells to radiotherapy. Based on this evidence, this trial includes oncological outcomes such as biochemical recurrence-free survival as secondary endpoints.

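### Neoadjuvant ADT and rectal spacer use are absent from the between-group factor list, so a difference in either could be credited to ALA-SFC in the secondary oncological and bowel comparisons

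*Protocol article*

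**What the plan says.** The trial is single-arm, and its comparator is a historical series from the same hospital. Section 2.4 (Determining the target sample size) names the characteristics to be compared between the two groups: "age, body mass index, comorbidities, pretreatment urinary frequency, pretreatment PSA level, pretreatment prostate volume, biopsy Gleason score, clinical tumor stage", followed by "D'Amico risk stratification, and the post-implant dosimetric parameters". Neither ADT nor spacer use appears.

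Elsewhere the article gives each of these co-treatments a role:

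- **ADT.** Section 2.1 says of trial patients that "those undergoing short-term (4–6 months) neoadjuvant androgen deprivation therapy (ADT) to decrease the prostate volume and/or improve oncological outcomes are included". Section 2.4 draws the controls from "consecutive patients undergoing LDR-BT with or without short-term ADT between January 2016 and January 2019". Use is therefore optional in both groups, and no proportions are stated.
- **Spacer.** Section 2.2 (Procedure of LDR-BT) says that, unless contraindicated, "SpaceOAR™ hydrogel is injected between the rectum and prostate to minimize high-dose radiation to the rectum and consequent bowel side effects". The definition of the controls does not mention it.

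The outcomes concerned are part of the trial. The Discussion states that "this trial includes oncological outcomes such as biochemical recurrence-free survival as secondary endpoints". Section 2.3 collects PSA, defines biochemical recurrence from PSA, and records CTCAE gastrointestinal toxicity and EPIC. Section 2.6 (Statistical analysis) plans two-group tests, Kaplan–Meier curves and the log-rank test.

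**The concern.** Without randomisation, any difference between the groups in a co-treatment that affects an outcome passes into the comparison unless it is restricted, matched, stratified or adjusted away. The article accepts this principle for two other treatments: section 2.4 removes controls who had prophylactic mirabegron or supplementary external-beam radiotherapy. For ADT and the spacer it states no restriction, and it does not list them among the factors to be compared.

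At stake is the reading of two groups of secondary results. A bowel benefit due to the spacer would look like the normal-tissue radioprotection that the Introduction gives as the rationale for ALA-SFC. An oncological difference due to ADT would look like the radiosensitisation that the Discussion gives as the reason for including oncological endpoints. Both would feed into the design of the planned randomised trial.

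**Working it through.** **1. The plan's own figure.** Section 2.4 assumes increases of 3 and 1 voids per day (difference 2), SD 3.5, a 1:3 ratio, two-sided α 0.05, 80% power and 10% ineligible.

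- Normal approximation: n(trial) = (1 + 1/3) × [3.5 × (1.960 + 0.842) / 2]² ≈ 32.05.
- t-test solution: 32.54 trial cases and 97.61 controls, rounded up to 33 and 98.
- Allowing for 10% ineligible: 33 / 0.9 = 36.7 → 37 and 98 / 0.9 = 108.9 → 109.

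These match the stated 37 and 109. At 50 and 150 the power is about 94%. This calculation concerns urinary frequency at 3 months and is not disputed.

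**2. The passages side by side.**

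| Co-treatment | Stated purpose | Outcome affected | Restricted in controls? | On factor list? | Adjustment stated? |
|---|---|---|---|---|---|
| Neoadjuvant ADT | Smaller prostate, better oncological outcome (2.1) | PSA, biochemical recurrence-free survival | No, with or without (2.4) | No | No (2.6) |
| Rectal spacer | Less rectal dose and fewer bowel effects (2.2) | CTCAE GI, EPIC bowel | No mention (2.4) | No | No (2.6) |
| Mirabegron prophylaxis | Less urgency and frequency (2.4) | Urinary outcomes | Yes, excluded (2.4) | n/a | n/a |
| External-beam radiotherapy | n/a | n/a | Yes, excluded (2.4) | n/a | n/a |

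**3. Size of the possible bias.** Let r be the event rate without the co-treatment, k its relative reduction, and p(T) and p(C) its use in trial cases and controls. If ALA-SFC has no effect, each group's rate is r × (1 − k × p), and the spurious difference is −r × k × [p(T) − p(C)]. The documents give none of these four inputs, so all values below are assumptions.

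*Assumption A: r = 20%, k = 0.5.*

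- Trial cases, 90% use: 20% × (1 − 0.45) = 11%.
- Controls, 60% use: 20% × (1 − 0.30) = 14%, a difference of −3 points.
- Controls, 30% use: 20% × (1 − 0.15) = 17%, a difference of −6 points.

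*Assumption B: r = 30%, k = 0.5, with 50 trial cases and 150 controls.*

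| Use, trial vs control | Rates | Spurious difference | Chance of a significant result favouring ALA-SFC |
|---|---|---|---|
| 90% vs 10% | 16.5% vs 28.5% | −12 points | about 38% |
| 90% vs 50% | 16.5% vs 22.5% | −6 points | about 13% |
| 60% vs 40% | 21% vs 24% | −3 points | about 6% |
| 50% vs 50% | 22.5% vs 22.5% | 0 | 2.5% (nominal) |

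The last column is Φ[(|d| − 1.96 × SE0) / SE1], where d is the spurious difference, SE0 the pooled and SE1 the unpooled standard error. For the first row, the pooled rate is (50 × 0.165 + 150 × 0.285) / 200 = 0.255, SE0 = 0.071 and SE1 = 0.064. This gives Φ(−0.30) ≈ 0.38. Fisher's exact test, which section 2.6 names for categorical variables, is more conservative, so its chances would be somewhat lower.

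The sign reverses if controls used the co-treatment more often. The same product of difference in use and effect governs ADT, but the documents give no effect size from which to illustrate it.

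**4. What the listed factors already cover.** Pretreatment prostate volume reflects part of what ADT does. The dosimetric parameters would carry the spacer's stated mechanism if rectal dose is among them, but the article does not itemise them. No listed factor represents ADT's stated oncological effect.

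**The case against.** The strongest reply has four parts.

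- **A journal article condenses the full protocol.** Covariates and adjustment may be set out in a document not shown, and the Tarone test named in section 2.6 could point to some stratified analysis. This stands as far as it goes. However, the article chose to give an explicit factor list without these two items, and it names no stratifying variable.
- **ADT is not ignored.** Eligibility is parallel in the two groups, sections 2.1 and 2.3 have medications recorded for trial patients, and section 2.6 promises descriptive statistics for all study variables. ADT data should therefore exist for trial cases. Recording it there does not secure the control data or place ADT in the comparison.
- **No imbalance is shown.** This stands. A reader might infer from the 2016–2019 control window that the spacer was new to the trial cases. Section 2.2 describes the hospital's procedure in general and gives no date of introduction, so the documents do not support that.
- **The list compares characteristics and is not an adjustment set.** This also stands. Adding two lines would reveal an imbalance without removing its effect.

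A reader might also infer that SHIM, EPIC and quality-of-life scores will drift as ADT wears off and be misread as a drug effect. The article gives ADT only the two purposes quoted from section 2.1 and says nothing of such recovery. The point does not rest on that argument.

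**Conclusion.** The point holds as a limitation of the secondary comparisons. The article attributes oncological and bowel effects to two co-treatments, yet neither restricts, lists nor adjusts for them against non-randomised controls. If their use differs, part of that difference can be reported as an effect of ALA-SFC on PSA and biochemical recurrence-free survival, or on gastrointestinal toxicity and EPIC bowel scores.

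The size is unknown. Under the assumptions above, the false bowel difference runs from 0 with equal use, through 3–6 points with moderate imbalance, to 12 points in an extreme case.

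Two stronger readings are not supported. One is that the secondary questions cannot be answered: that would follow only if use proves imbalanced or cannot be established. The other is that adjusting for the listed factors would achieve nothing: prostate volume, and rectal dose if included, give partial cover. The documents state no effect of the spacer on urinary frequency, and the primary endpoint and sample size are not challenged.

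**What to change.** 1. Add neoadjuvant ADT (yes/no, duration) and spacer use (yes/no) to the factor list in section 2.4. Extract both for the controls from the hospital's records and report them by group.
2. Stratify or adjust the bowel comparison (CTCAE GI, EPIC bowel) by spacer status.
3. Stratify or adjust the PSA and biochemical recurrence comparison by ADT. As a sensitivity analysis, do the same for SHIM and the EPIC sexual and hormonal scores.
4. If too few controls share the spacer status of the trial cases, report bowel outcomes descriptively, without a between-group claim.
5. State whether rectal dose is among the dosimetric parameters.

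The cost is two variables from one hospital's own records and some additional tables. The downside is smaller strata and wider intervals for these secondary outcomes. The primary analysis and the target numbers stay as they are.
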